| Recruitment status      | Planning                                                                                                                                                                                                                                                                                                                                                                                                                                                        |                              |
| Primary outcomes        | 24-hour intravenous crystalloid fluid administration                                                                                                                                                                                                                                                                                                                                                                                                            |                              |
| Key secondary outcomes  | Feasibility measures: 
 
• Number of patients with major protocol violations,
 
• Number of patients screened vs included
 
• Time from admission to inclusion
 
• Number of patients lost to follow up in terms of 24-hour fluids
 
• Accumulated serious adverse reactions and events (SARs + SUSARs) within 48 hours in-hospital
 
 Total fluids (oral and intravenous) at 24 hours, |                              |

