### 3. TRIAL DESIGN

#### 3.1 Overview

This is an investigator-initiated, multicenter, randomized, parallel-group, open-labeled, feasibility trial investigating volumes of fluid within 24 hours in 124 patients with sepsis allocated to two different IV fluid regimens enrolled at three emergency departments in Central Region Denmark. The objective is to assess the feasibility of a trial comparing two approaches to intravenous fluid resuscitation of sepsis; a restrictive approach using four criteria vs. standard care. The hypothesis is that the restrictive approach is feasible and will result in less IV fluid given. The primary outcome is total intravenous fluid volume within 24 hours and key secondary outcomes include protocol violations, total fluids (intravenous and oral) within 24 hours, progression to septic shock, and SAEs/SUSARs.

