#### **5.2 Secondary outcomes**

##### *5.2.1 Definitions*

The secondary outcomes will be

- Feasibility measures:
  - Number of patients with major protocol violations,

- Number of patients screened positive (ie.with all inclusion criteria fulfilled and no exclusion criteria fulfilled) vs randomized
- Time from admission to inclusion
- Number of patients lost to follow up in terms of 24-hour fluids (e.g. due to discharge within 24 hours)
- Accumulated serious adverse reactions and events (SAEs + SARs+ SUSARs) within 7 days in-hospital
- Total fluids (oral and intravenous) at 24 hours

We will also report in-hospital mortality and 30- and 90-day mortality (possible outcomes for the final large scale trial), in-hospital length of stay (LOS), mechanical ventilation within 7 days of admission (yes/no), vasopressor use within 7 days of admission (yes/no), and development or worsening of acute kidney failure according to the KDIGO3-criteria within 7 days of admission (also an SAE, see above) .

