#### *5.4.3 Assessment of adverse events*

##### *Timing*

In all participants, we will assess the occurrence of SARs in the 7 days following randomization (the intervention period is 24 hours; 7 days allow for another 6 days of assessment after the intervention, which is clinically relevant in critically ill patients).

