#### *5.4.5 Definitions of Suspected Unexpected Serious Adverse Reaction (SUSAR) in REFACED Sepsis*

SUSARs will be defined as serious reactions not described in the Summaries of Product Characteristics for the used crystalloids happening within 7 days of admission if not otherwise stated. Suspected Unexpected Serious Adverse Reactions (SUSAR) will be reported to the regulatory authorities as applicable.

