#### *7.1.6 Variables obtained at 6-, 12- and 24 hours after randomization:*

Hourly volumes of resuscitation fluid with specification of indication for each fluid bolus

Other fluids including blood products, nutrition, fluid with medication

Highest creatinine within 24 hours to evaluate KDIGO-criteria

Only 24hours: To evaluate worst SOFA-score within 24 hours:

Results of blood samples (standard lab. Values + arterial/venous blood gas)

- Lowest values: platelets, PaO2 (and FiO2)
- Highest values: lactate, bilirubin,

Use of renal replacement therapy Y/N

Protocol violations

Non-invasive ventilation Y/N

On mechanical invasive ventilation or vasopressor Y/N

Status: dead, Y/N

Only 24hours: SAEs (see section 5.4.3) + SARs (see section 5.4.4)

SAEs on this day (y/n for everyone)

- Cerebral ischemic event
- Myocardial ischemic event
- Intestinal ischemic event
- Limb ischemia
- New onset of severe acute kidney injury

SARs on this day (y/n for everyone)

- General tonic-clonic seizures
- Anaphylactic reactions
- Central pontine myelinolysis
- Severe hyponatremia
- Severe hyperchloremic acidosis
- Severe metabolic alkalosis

Only 24 hours: SUSARs

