#### *7.1.7 Variables on every day until 7 days from enrollment*

On mechanical invasive ventilation or vasopressor Y/N

SAEs (see section 5.4.3 + see above)

SUSARs (see section 5.4.5)

Status: dead, Y/N

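### The safety outcome is worded three ways in current text, and the daily variable list does not secure the 7-day version

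*Protocol*

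**What the plan says.** The safety outcome appears in three places in the protocol:

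- Section 5.2.1 (secondary outcomes): "Accumulated serious adverse reactions and events (SAEs + SARs+ SUSARs) within 7 days in-hospital".
- Overview table (key secondary outcomes): "Accumulated serious adverse reactions and events (SARs + SUSARs) within 48 hours in-hospital".
- Section 3.1 (design overview), at the end of its list of key secondary outcomes: "progression to septic shock, and SAEs/SUSARs".

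On timing, section 5.4.3 states that "we will assess the occurrence of SARs in the 7 days following randomization", and Appendix 3 also runs from randomization to day 7. Section 5.4.5 instead counts SUSARs as events "happening within 7 days of admission if not otherwise stated". Section 5.2.1 also uses admission as the origin for ventilation, vasopressor use and kidney failure within 7 days.

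On data, section 7.1.6 has the line "Only 24hours: SAEs (see section 5.4.3) + SARs (see section 5.4.4"), followed by a checklist of five SAEs and a separate checklist of six SARs. Section 7.1.7, the daily list to day 7, has "SAEs (see section 5.4.3 + see above"), a SUSAR line, vital status and "On mechanical invasive ventilation or vasopressor Y/N". It has no SAR line and does not cite section 5.4.4, where the SARs are defined.

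**The concern.** What counts as an outcome, and over which days, belongs in the protocol. Here two explicit definitions conflict and a third is incomplete. The trial is open-label (section 3.4). Section 5.4.1 relies on the secondary outcomes to capture harm, and section 5.2.2 wants the additional outcomes for powering the large trial. While more than one definition stands, the window and the components could be settled after the data are known, and a reader of the report could not tell which was planned.

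The second problem is capture. If abstraction follows the listed variables, SARs are asked about once, at 24 hours, although section 5.4.3 promises 7 days. Any resulting under-count would carry into the comparison between arms and into the rates passed to the next trial.

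**Working it through.** The plan gives no figure for this point, so the check sets the sections side by side.

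**1. Definition of the outcome**

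| Place | SAEs | SARs | SUSARs | Window |
|---|---|---|---|---|
| Overview table | no | yes | yes | 48 hours, in hospital |
| Section 3.1 | yes | not named | yes | none given |
| Section 5.2.1 | yes | yes | yes | 7 days, in hospital |

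No two rows agree on components, and no two agree on window. None of the three is an amendment log. In hours, 48/168 = 0.286, so the Overview version covers 29% of the 7-day window, or 2 of 7 days, and leaves 5 days out.

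**2. Time origin**

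- Randomization: section 5.4.3 (SARs and SAEs) and Appendix 3.
- Admission: section 5.4.5 (SUSARs), and section 5.2.1 for ventilation, vasopressor use and kidney failure.
- Enrollment: the heading of section 7.1.7.

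Section 4.2 sets no maximum time to inclusion but expects it within the first couple of hours. The shift is therefore expected to be hours in a 7-day window: real, but small.

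**3. SARs in the variable list**

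Section 7.1.6 keeps SAEs and SARs in separate blocks. The five SAE items are four kinds of ischemic event and new severe kidney injury. The six SAR items are seizures, anaphylaxis, pontine myelinolysis, and the sodium, chloride-acidosis and alkalosis events. The blocks do not overlap, so carrying the SAE block forward does not carry the SARs.

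Section 7.1.7 carries forward SAEs and SUSARs only. On the listed variables, SARs are itemised on day 1 of 7: 24/168 = 14% of the window, leaving 86% (6 days) without an explicit item. Myelinolysis shows the mismatch most clearly. Section 5.4.4 defines it over the 7 days after randomization, yet its only listed item is at 24 hours.

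**4. Lesser mismatches**

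- Ventilation and vasopressor use are two outcomes in section 5.2.1 but one either/or item in section 7.1.7.
- Kidney failure in section 5.2.1 covers development or worsening over 7 days. New severe kidney injury is on the SAE checklist that section 7.1.7 refers back to. Worsening of an existing injury has no listed item after 24 hours, because highest creatinine is listed only up to then.
- Progression to septic shock is a key secondary outcome in section 3.1 but does not appear in section 5.2.1.

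**The case against.** The strongest reply is that a missing summary line is not missing data. No case report form is shown. Section 7.1.2 describes the lists as a summary and leaves the detail to a data dictionary. Section 5.4.3 and Appendix 3 commit to SARs through day 7. The back-reference in section 7.1.7 could be read as covering the whole 24-hour block, whose checklists are worded per day. Section 5.4.6 gives another route: SAEs not listed in Appendix 3 go to the sponsor within 24 hours, and the named SARs are not on that list. Laboratory-defined SARs could also be retrieved from the medical record.

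This stands against several stronger conclusions that a reader might draw:

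- **That the forms stop collecting SARs after 24 hours, or that the 7-day outcome cannot be produced.** The document does not show this. It shows only that the list does not guarantee capture.
- **That separate ventilation and vasopressor outcomes cannot be recovered.** Section 5.2.2 gives each its own daily definition, and the source records hold both, so the combined line may be shorthand.
- **That kidney failure is untracked after 24 hours.** Only worsening lacks an item.
- **That the outcome should count patients with at least one event instead of accumulated events.** That is a preference and corrects no error.

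The sections that define and time the outcome also favor 7 days. The amendment list records that event timing and Appendix 3 were revised in version 1.2, so an Overview row left unrevised is a plausible explanation.

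What the reply does not remove:

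- The conflict in definition needs no form to be seen, and a plausible origin does not resolve it.
- The dictionary is described as elaborating these same lists, and section 7.1.2 intends few variables, so nothing assures that an omitted block will be added.
- Expedited reporting depends on someone recognizing the event as an SAE. Several SARs in section 5.4.4 are bare laboratory thresholds, and a value past the threshold need not meet the seriousness criteria in section 5.4.2.

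**Conclusion.** The point holds as an internal inconsistency in a secondary safety outcome. Three current statements disagree on components and window, 48 hours against 7 days where a window is given. The origin switches between randomization and admission, with an expected effect of hours. The variable list itemises SARs on 1 of the 7 days promised.

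Under-counting of SARs on days 2 to 7 is a risk, not an established loss. It rests on the assumption that abstraction follows the list as printed. If the data dictionary already repeats the SAR checklist daily, the capture problem disappears and only the wording needs correcting. The conflict between the Overview, section 3.1 and section 5.2.1 remains either way. The primary outcome and the sample size of 124 are untouched.

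**What to change.** - Align the Overview table and section 3.1 with section 5.2.1: SAEs, SARs and SUSARs over 7 days, counted from randomization.
- Use the same origin in section 5.4.5 and for the ventilation, vasopressor and kidney outcomes in section 5.2.1.
- Add the section 5.4.4 SAR checklist and creatinine to the daily list in section 7.1.7.
- List ventilation and vasopressor use as two items.
- Either add progression to septic shock to section 5.2.1 with the data it needs, or remove it from section 3.1.

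The cost is protocol wording and a few extra fields per patient-day, abstracted from records that the research team already consults for the daily variables to day 7. No trial treatment or visit changes.

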#### *5.2.2 Elaboration on secondary outcomes*

The study is a feasibility trial only powered to answer the primary aim. However, we regard the above mentioned as important feasibility measures. The trial will include additional outcomes focused on hemodynamics, organ failure, and long-term outcomes in order to be able to power calculate for the planned large-scale trial.

Both 30-day and 90-day survival will be obtained from electronic medical records or the Danish Civil Personal Register which allows for accurate and virtually complete follow-up.

We will include 90-day survival as a measure of long-term survival. 90 days were chosen since it is unlikely that mortality later than that will be directly linked to the sepsis event or the trial interventions.

A vasopressor will be defined as any continuous infusion of noradrenaline, dopamine, dobutamine, terlipressin, vasopressin, phenylephrine, and/or adrenaline. Receiving vasopressors for a total of at least 3 hours on a given day is defined as receiving vasopressors for that day. Invasive ventilation is defined as mechanical ventilation through an endotracheal or tracheostomy tube, not only used for surgery for a total of at least 3 hours on a given day.

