### **6.2 Statistical analysis plan**

#### *6.2.1 General considerations*

The statistical reporting will adhere to the CONSORT guidelines. All tests will be two-sided, a p-value < 0.05 will be considered significant, and all confidence intervals will have 95% coverage.

Patient inclusion and exclusion will be illustrated in a CONSORT flow diagram (see Appendix 7 for a draft).

We will include measures related to feasibility including the enrolled to screened ratio, time to randomization, and protocol adherence/major protocol violations. All analyses will be conducted in the intention-to-treat (ITT) population defined as all randomized participants for whom consent was obtained. We will perform the primary analyses adjusted for the stratification variable site.

The two groups will be compared in relation to baseline patient and sepsis characteristics using descriptive statistics.

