#### *6.2.2 Primary and secondary outcomes*

To estimate the mean difference in fluid volume between groups, we will use linear regression with adjustment for the stratification variable. If the data is severely non-normally distributed, we will consider other appropriate options (e.g., "robust standard errors" or transformation). Other continuous variables will be analyzed similarly. For binary outcomes, we will use logistic regression adjusted for site and results will be presented as odds ratios.

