#### *6.2.3 Missing data*

Missing data will be reported in the relevant publications. We do not expect any missing data for the primary outcome (except for those discharged within the 24 hours) or the key secondary outcomes. Patients discharged within 24 hours or who died within 24 hours, will be included in the ITT analysis with the amounts they received until discharge/death. We do not expect missing data on mortality or adverse events. Multiple imputation using known risk factors for outcomes in sepsis will be used to impute values for patients with missing data if missing data is substantial (> 10%).

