Participants will be asked for informed consent as soon as possible after they regain the ability to provide consent. For participants, both oral and written information will be given preferably in person. The participant has the right to bring a companion.

If a patient dies before it is possible to obtain consent (we anticipate that approximately 6% will die in-hospital as found in our yet unpublished study), patient data will be included in the trial. If a patient denies

future participation in the trial, no additional data will be collected but all data collected up until the point of withdrawal will be included consistent with Danish law.

The abovementioned trial-specific procedures are in accordance with current trials enrolling patients in Denmark: CLASSIC trial (ClinicalTrials.gov Identifier: NCT03668236) conducted in the ICU and HOT-COVID (ClinicalTrials.gov Identifier: NCT04425031) and COVID-steroid 2-trial (VEK nr. H-20051056, EudraCT nummer 2020-003363-25, ClinicalTrials.gov Identifier: NCT04509973) conducted in all hospital departments with COVID-19 patients.

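### The 7-day ventilation, vasopressor and kidney outcomes take no account of death, so they understate harm in an arm that has more early deaths

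*Protocol*

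**What the plan says.** Section 5.2.1 of the protocol lists, after the bulleted secondary outcomes, "mechanical ventilation within 7 days of admission (yes/no), vasopressor use within 7 days of admission (yes/no". The same sentence adds a kidney outcome, KDIGO3 failure that develops or worsens over the same 7 days. It is not itself marked yes/no, but it is binary as worded. Section 5.2.2 sets a daily threshold, "Receiving vasopressors for a total of at least 3 hours on a given day", with a similar one for invasive ventilation, and does not mention death.

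Section 6.2.2 gives the analysis: "For binary outcomes, we will use logistic regression adjusted for site and results will be presented as odds ratios". Section 6.2.1 runs all analyses in the "intention-to-treat (ITT) population defined as all randomized participants for whom consent was obtained". Section 9.3.2 keeps the data of patients who die before consent can be obtained, so early deaths are meant to stay in the comparison.

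The only analysis rule for death is in section 6.2.3. It concerns fluid volume and the first day: patients "who died within 24 hours, will be included in the ITT analysis with the amounts they received until discharge/death". Mortality is reported in hospital and at 30 and 90 days (5.2.1). Section 7.1.7 records "Status: dead, Y/N" every day to day 7.

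**The concern.** Under these definitions a patient who dies on day 2 without ventilation, vasopressors or KDIGO3 kidney failure is scored *no* on all three outcomes, exactly as a patient who goes home well. Death removes the chance of a later event. If fluid restriction affects early death in either direction, the amount removed differs by arm.

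Two statements in the protocol give this some weight. Section 5.4.1 relies on the secondary outcomes to capture benefit and harm, and section 5.2.2 wants organ-failure outcomes for the power calculation of the large trial. Section 1.2.3 itself says that restriction may compromise perfusion, so an arm difference in early death cannot be ruled out beforehand. Exclusion 6 in section 4.3 removes only patients not expected to survive 24 hours, and limits on escalation are not an exclusion. An outcome that responds weakly to deaths is a poor harm signal when read alone, and a poor planning input.

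**Working it through.** **The plan's own figures.** The sample size concerns only the primary outcome. With a difference of 1000 ml, SD 1700 ml, two-sided alpha 5% and power 90%, the two-sample t-test needs 61.7, so 62 per arm and 124 in total, as section 6.1 states. This point does not touch that number.

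For deaths, section 9.3.2 says "we anticipate that approximately 6% will die in-hospital as found in our yet unpublished study". That gives 0.06 × 124 = 7.4 deaths in all, or 0.06 × 62 = 3.7 per arm. Only deaths by day 7 and without the event matter here, so about 7 is a ceiling.

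**Assumptions.** The protocol gives no organ-support rates and no 7-day mortality. Let r be the event risk in 7-day survivors (the same in both arms), d the 7-day death risk in an arm, and q the share of dying patients who have the event first.

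- Plain yes/no risk = (1 − d)r + dq
- Event-or-death risk = (1 − d)r + d
- Plain difference between arms = (d1 − d0)(q − r)
- Event-or-death difference = (d1 − d0)(1 − r)

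The third line settles the direction. The plain difference points against the arm with more deaths when q > r. It favours that arm only when q < r, that is, when dying patients receive support less often than survivors. If d1 = d0, both differences are zero.

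**Illustration with r = 10%, deaths 10% versus 3%.**

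| q | Plain, 10% deaths | Plain, 3% deaths | Plain difference | Event-or-death difference |
|---|---|---|---|---|
| 0 | 9.0% | 9.7% | −0.7 points | 19.0% − 12.7% = 6.3 points |
| 1/3 | 12.3% | 10.7% | +1.6 points | 6.3 points |
| 1/2 | 14.0% | 11.2% | +2.8 points | 6.3 points |

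The part of the 6.3 points that the plain outcome does not show is (1 − q)/(1 − r): 111%, 74% and 56% in the three rows. At q = 0 the reversal of 0.7 points is 0.007 × 62 = 0.4 patients.

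**Other assumed rates.**

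- Deaths 8% versus 4%, r = 10%: the plain difference is 0.04 × (q − 0.10) = −0.4, +0.9 or +1.6 points, against 0.04 × 0.90 = 3.6 points for event or death.
- Deaths 9% versus 3%, r = 5%, 10% or 15%, q = 0: the plain odds ratios (more deaths versus fewer) are 0.94, 0.93 and 0.93. For event or death they are 1.84, 1.52 and 1.38.
- The same with q = 1/2: the plain odds ratios are 1.47, 1.25 and 1.16.
- Deaths 6% in both arms: every odds ratio is 1.00.

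These scenarios are at the high end. The first averages 6.5% death within 7 days, above the protocol's 6% for the whole hospital stay. The other two average 6%, which places every in-hospital death inside the first week.

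**The case against.** The strongest reply is that nothing is miscoded. A patient who died without vasopressors did not use them, so *no* is true. With complete follow-up, the proportion with the event is the cumulative incidence with death as a competing event, which is a legitimate quantity when read beside mortality. This stands, and it is why the stated outcomes should be kept.

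Second, death is not hidden. Mortality is reported, and death is a serious adverse event that enters the 7-day count. This stands in part. None of those figures is 7-day mortality on its own, and separate totals do not show how many of the patients scored *no* had died. That needs the joint count.

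Third, section 12 announces an article with the statistical analysis plan, which could add a rule. It could. But the protocol already fixes the outcome, the window and the model, and where it does address early death in the analysis it writes a rule for fluid volume only.

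Fourth, much of the 6.3 points is simply the assumed 7-point mortality gap carried into the composite. That is correct, and it argues for showing components rather than replacing the outcomes.

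A reader might go further and infer that the arm with more deaths will look better. The documents do not support that. It needs q < r, and they give no figures on support before death or on treatment limits. Dementia and frailty are only recorded baseline variables (7.1.3). The 3-hour threshold would lower q somewhat if applied to the yes/no outcome, but by an unknown amount.

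**Conclusion.** The point holds in a limited form. The three outcomes ignore death as a competing event, so with unequal early deaths they understate harm in the arm with more deaths, compared with event or death. Under the main assumed rates they show between −0.7 and +2.8 points where event or death shows 6.3. All these sizes rest on assumed survivor rates, assumed 7-day deaths and an unknown q. Dilution is the likely form of the problem; reversal is a special case worth less than one patient per arm in the scenarios shown.

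The stakes are modest. These are additional outcomes in a feasibility trial powered only for fluid volume, few deaths are expected, and the primary result is unaffected. The issue matters mainly for reading harm and for planning the large trial. It justifies a small amendment and does not call the design into question.

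**What to change.** In sections 5.2.1 and 6.2.2, keep the three stated outcomes and their logistic model. Then:

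- add, for each, event or death within 7 days as a supplementary between-arm comparison;
- show by arm the number with the event, the number who died within 7 days, and the number who died within 7 days without the event;
- state that these joint figures will be used when an organ-support outcome is considered for the large trial.

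The cost is a sentence or two in each section and a few table rows. No new data are needed, because section 7.1.7 already records vital status daily to day 7. That record runs from enrollment while the outcomes run from admission, so the text should name one starting point for both parts of each composite.

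The downside is small: the three composites share the same few deaths and are partly driven by mortality. The component rows make this visible.
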